### C. Transcranial Duplex Scanning (TCD)

TCD investigation is performed bilaterally through the pre-auricular bone window with a 2–4 MHz phased array transducer (SONOS 5500; Philips, Eindhoven, the Netherlands) by an experienced sonographer, blinded for the clinical data and SPECT results. The quality of the temporal bone window, the SN and Raphe nuclei (RN) of all subjects are scored directly by the sonographer blinded for the final clinical diagnosis and SPECT result. The quality of the bone window is scored as good, moderate or inconclusive.

Two different methods are applied for the evaluation of the echointensity of the SN. Firstly, the presence or absence of an obviously visible bilateral hyperechogenic SN is scored (qualitative method). The SN are scored as hyperechointens, not hyperechointens or inconclusive (= no typical configuration of hyperechointensity or low quality of the temporal bone window). Secondly, the area of an eventually hyperechogenic SN will be measured quantitatively (quantitative method). Both the right and left SN are measured from both sides, i.e. both temporal bone windows. After encircling, the area is automatically calculated. A hyperechogenic area of at least 0.2 cm^2 ^is classified as characteristic for PD. The RN are scored as: invisible (= iso-intense), just visible, visible (= hyper-intense) or inconclusive (= doubtful echointensity or low quality temporal bone window).

To determine inter-observer variability and to increase the power of the study a second sonographer will also judge the acquired echo data. A loop of 64 images of each patient will be acquired scanning the brainstem cranio-caudally and will be stored in order to allow for off-line analysis. Off-line the quality of the temporal bone window, SN and RN will scored by the second sonographer.

### D. Regular Outpatient follow-up

The initial treating neurologist will remain responsible for the regular outpatient management of the patient included in the study. He or she will discuss the test results with the patient, and base his/her treatment plan on these. All further clinical decisions will be made by the treating neurologist.

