### A. Interview and neurological examination

After informed consent the patient is seen on the outpatient clinic for the inclusion interview and neurological examination by a third party physician (i.e. a physician not treating the patient, and blinded for information in the routine clinical records). In the structured interview a standard form with the following items are discussed: medical history, used drugs and effect, intoxications, duration of complaints, and most affected body- side (See attachment 1). The following clinimetric scales are scored: UPDRS (parts I, III and IV) [32], Hoehn and Yahr score [33], Hamilton Rating Scale [34] for depression and the SCOPA cognition scale [35]. The Sniffin Sticks smell test is done according to a standardised protocol [36,37]. Finally, the including physician will try to reach a probable diagnosis, strictly applying the UK Parkinson's Disease Society Brain Bank criteria [2].

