### E. Re-examination at two-year follow-up

Two years after inclusion, all patients will be re-examined separately by two independent movement disorder specialist neurologists blinded for the tests results. They will also be blinded for the clinical records of the treating neurologist. The same standard form as in the first visit is filled in (see Additional file 1) and they will be asked to reach a clinical diagnosis, independently from each other, according to generally accepted clinical criteria [38-44]. If these two diagnoses are not identical, the final diagnosis of this patient will be coded as inconclusive.

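### Patients are told their test results and treated on them, so the two-year reference diagnosis is open to indirect influence from SPECT and TCD despite the stated blinding

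*Protocol article*

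**What the plan says.** Under Methods and Data analysis, the protocol article makes the two-year clinical diagnosis the reference standard for the accuracy of both TCD and SPECT. Three sections govern how that diagnosis is reached.

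- **Section D (regular outpatient follow-up)**, on the treating neurologist: "He or she will discuss the test results with the patient, and base his/her treatment plan on these".
- **Section E (re-examination at two years)**: all patients are "re-examined separately by two independent movement disorder specialist neurologists blinded for the tests results". On the treating physician's notes it adds: "They will also be blinded for the clinical records of the treating neurologist". On the data collected: "The same standard form as in the first visit is filled in".
- **Section A (interview and examination)** describes that form. Its interview items are "medical history, used drugs and effect, intoxications, duration of complaints, and most affected body- side".

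The Discussion concedes that misdiagnosis at two years remains possible. Its answer is to require agreement between two independent, blinded specialists.

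**The concern.** Section E shuts off two sources of information for the assessors: the test reports and the treating neurologist's file. A third source stays open. By the time of the two-year visit the patient has been told the results and has been treated in the light of them. The assessors interview this patient and record which drugs were taken and what they did. A patient can mention a scan result unprompted, and the drug history may itself hint at it.

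If that information moves a diagnosis towards agreement with a test, the test is partly being compared with its own consequences. Errors of the test disappear from the two-by-two table, and its sensitivity and specificity look better than they are. The agreement rule gives little protection, because both specialists see the same patient with the same drug history and can be moved in the same direction.

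**Working it through.** **The sections side by side**

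1. Result to patient: stated in section D.
2. Result to treatment: stated in the same sentence of section D.
3. Patient and treatment to assessor: section A puts drugs and their effect on the form, and section E has the same form completed at two years.
4. Assessor to reference standard: stated under Methods and used under Data analysis.

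Each link is in the text. The article describes no step that interrupts links 1 to 3; the exclusion of the treating neurologist's records in section E closes a different route. Additional file 1 is not shown, so the content of the form is taken from section A.

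**Size, as an illustration**

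The plan gives no figure for this bias, so there is none to reproduce. Inputs:

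- true sensitivity Se = 0.90, the value Data analysis assumes for SPECT and TCD;
- c = share of PD patients with a false-negative result whose reference label becomes non-PD. This is an assumption, shown at 10%, 20% and 30%.

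Relabelled patients leave the denominator, and the numerator is unchanged:

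apparent Se = Se / [Se + (1 − Se)(1 − c)]

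- c = 10%: 0.90 / (0.90 + 0.10 × 0.90) = 0.90 / 0.99 = 90.9%
- c = 20%: 0.90 / (0.90 + 0.10 × 0.80) = 0.90 / 0.98 = 91.8%
- c = 30%: 0.90 / (0.90 + 0.10 × 0.70) = 0.90 / 0.97 = 92.8%

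**Relabelling in both directions**

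Now let a share c of all discordant patients, false positives included, be moved to agree with the test. Take PD prevalence 90% (Data analysis) and specificity 80% (assumed). Per patient enrolled, TP = 0.81, FN = 0.09, TN = 0.08, FP = 0.02.

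apparent Se = (TP + c·FP) / [TP + c·FP + (1 − c)·FN]

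apparent Sp = (TN + c·FN) / [TN + c·FN + (1 − c)·FP]

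| c | apparent Se | apparent Sp |
|---|---|---|
| 10% | 0.812 / 0.893 = 90.9% | 0.089 / 0.107 = 83.2% |
| 20% | 0.814 / 0.886 = 91.9% | 0.098 / 0.114 = 86.0% |
| 30% | 0.816 / 0.879 = 92.8% | 0.107 / 0.121 = 88.4% |

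Sensitivity hardly differs from the one-way case. Specificity moves more, because at 90% prevalence the non-PD group is small and a few relabelled PD patients weigh heavily in it.

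**What happens to the other test**

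Suppose SPECT steers the label and c = 30%. Then 3% of the PD patients, all SPECT-normal, are lost from the PD group. With TCD sensitivity also 90%, the effect on TCD depends on how many of these patients are TCD-positive:

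- 90% (misses independent): (0.90 − 0.027) / 0.97 = 0.873 / 0.97 = 90.0%
- 50%: (0.90 − 0.015) / 0.97 = 0.885 / 0.97 = 91.2%
- none (same patients missed by both): 0.90 / 0.97 = 92.8%

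So the other test may gain nothing, something or just as much. The documents say nothing about the overlap.

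**The case against.** The strongest case on the other side has four parts.

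**The text shows a risk, not a fact.** Section E instructs the assessors to be blind and keeps the treating neurologist's records from them. A reader might infer that the reference diagnosis is contaminated and the blinding void. The documents do not support that: they show an open route and say nothing about how often it changes a diagnosis. By year two, medication also reflects two years of clinical course and decisions, so it is not a direct trace of the scan. This objection stands, and the point is worded accordingly.

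**Drug response is genuine diagnostic information.** A poor response to treatment begun after a false-positive test could move the diagnosis away from the test. Neither test is a component of the reference diagnosis, so this is indirect unblinding and not incorporation in the strict sense. This also stands: inflation is probable, not certain. It is why the informed diagnosis should stay primary.

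**The direction between tests is unknown.** A reader might infer that SPECT is favoured, because the Background calls it the most widely used tool. Section D does not rank the tests. Table 1 points the other way for PD against MSA and PSP: SPECT is expected to be equally abnormal in all three, while TCD is expected to be clearly abnormal in PD and only equivocal in MSA and PSP. TCD could steer the label at least as much.

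**The full protocol may contain safeguards.** It may, and their absence from an article would be no finding. The point rests on what sections A, D and E affirmatively describe; a safeguard elsewhere would have to be squared with them.

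**Conclusion.** The point holds as a risk to the reference standard. Section E claims blinding to the test results. Sections A and D describe a route by which those results can reach the assessors, through the informed patient and through the drug history. The Discussion relies on the blinding without addressing this route. The apparent accuracy of whichever test steers management would probably be inflated.

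The size cannot be derived from the documents. With an assumed 10% to 30% of false-negative PD patients relabelled, a true 90% sensitivity appears as 90.9% to 92.8%. The effect on the TCD-versus-SPECT comparison has no known sign, and it vanishes if the two tests miss the same patients.

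A reader might set the 2.8-point rise against the 4 points between 90% and 86% under Data analysis and conclude that most of the tolerance is gone. That comparison is not valid. The 86% is the lowest acceptable confidence limit for TCD sensitivity, not a margin between the two tests, and the 90% for SPECT comes from earlier data.

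**What to change.** Reconcile sections D and E, leaving patient care and disclosure of results by the treating neurologist as they are.

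1. Ask patients not to reveal test results to the reference neurologists. Record on the two-year form any disclosure that occurs and each assessor's guess of the TCD and SPECT results.
2. Have each assessor record one diagnosis before seeing the drug section and a second after it. Keep the second, fully informed diagnosis as the primary reference standard, and use the first in a prespecified sensitivity analysis.
3. Report accuracy in all patients and, as a sensitivity analysis only, excluding those whose assessor was unblinded.

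The cost is a reordered form, one instruction to patients, a few extra items and two extra analyses. There are limits to state openly. The first diagnosis is less informed, and it is not free of treatment effects, because treatment also alters the signs and symptoms being examined. The analysis without unblinded patients may be selective. Neither analysis removes the bias; together they show whether the main result is sensitive to it.

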### E. Re-examination at two-year follow-up

Two years after inclusion, all patients will be re-examined separately by two independent movement disorder specialist neurologists blinded for the tests results. They will also be blinded for the clinical records of the treating neurologist. The same standard form as in the first visit is filled in (see Additional file 1) and they will be asked to reach a clinical diagnosis, independently from each other, according to generally accepted clinical criteria [38-44]. If these two diagnoses are not identical, the final diagnosis of this patient will be coded as inconclusive.

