**Methods/Design:**

We will enrol 250 consecutive patients, who are referred to neurology outpatient clinics of two teaching hospitals, for analysis of clinically unclear parkinsonism. Patients, whose parkinsonism is clearly diagnosable at the first visit, will be excluded from the study. All patients will undergo a TCD of the substantia nigra. As a surrogate gold standard we will use the consensus clinical diagnosis reached by two independent, blinded, movement disorder specialist neurologists after 2 years follow-up. At the time of TCD, patients will also undergo a SPECT scan of the brain.

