#### Exclusion criteria

1. Patients presenting with a clear unequivocal diagnosis of their parkinsonism.

2. Patients whose life expectancy is less than the required follow-up of two years.

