### Data analysis

Our main hypothesis is that TCD is as sensitive as SPECT to differentiate PD from other parkinsonian disorders. For the power analyses we assumed a sensitivity of SPECT of 90%, based on the analysis of our own data on 248 consecutive patients [19]. Assuming this 90% for TCD sensitivity we can accept as lowest border of the 95% confidence interval, 86% or higher:

*SD *= (√ (p1 (1-p1))/n → p1 = 0.9, sd 0.02, implying n = 190 patients, needed who have the hyperintensity of SN with TCD scanning.

In our pilot study 15% of the patients had an insufficient temporal bone window, so 224 patients are needed to compensate for the amount of inconclusive TCDs [28]. Based on this study we expect that 90% of all patients with inconclusive parkinsonism will ultimately have PD, so we set a target of initial 250 patients with unclear parkinsonism needed for this trial. We will calculate the sensitivity and specificity, positive predictive value, negative predictive value and diagnostic odd's ratio (OR) with its 95% confidence intervals (95% CI) of the first clinical judgment, TCD, FP-CIT SPECT scan and smell tests to predict the clinical diagnosis after 2 year follow-up. Accuracy is determined for all parkinsonian subgroups separately (PD versus APS, PD versus ET, and PD versus VP, PD versus DIP, and PD versus all other types of parkinsonism). For expected SPECT, TCD and smell tests scores for each parkinsonian disorder, see table 1.

**Table 1 T1:** Expected TCE, FP-CIT SPECT and odour recognition results for all parkinsonian disorders

Disease	FP-CIT SPECT abnormal, [19, 46]	abnormal SN TCD [47]	odour recognition deficit	cognition deficit
IPD	++	+++	+++	±
ET	Normal	normal	normal	normal
VP	normal *	normal	normal (?)	±
DIP **	normal (+)	normal (+)	normal (+)	normal (±)
MSA	++	±	+	±
PSP	++	± (?)	normal (±)	++

= normal FP-CIT tracer binding ratios

↓: FP-CIT binding of at least 2 sd. below healthy controls

* especially visual judgement together with CT or MRI

** At least 10% percent of the patients with DIP will develop to the PD [48]. So some patients in early stages of PD can theoretically present as DIP. Berg et al. investigated the relation between echointensity of SN on TCD and DIP after the start of antipsychotic drugs. Patients with serious parkinsonism scored higher echointensity as patients with mild or no parkinsonism [47].

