## Discussion

The hitherto published literature on TCD in parkinsonian syndromes are cross-sectional studies on clinically well-defined patient populations [20-30,45]. Although one has to start with these to study the diagnostic potential of a new technique, these kind of studies are obviously not representative of the clinical problem that one wants to solve with a TCD in parkinsonian syndromes. The treating neurologist wants a diagnostic tool that provides additional information in patients with a clinically indefinable parkinsonian syndrome.

The above described observational longitudinal study was designed to explicitly study this aspect in the diagnostic process. We arbitrarily choose the clinical diagnosis after two years as the surrogate gold standard. This is, of course, not ideal, as there will always remain a small proportion of patients that is not definitely diagnosable after two years, and misdiagnoses (as opposed to the ultimate gold standard the post-mortem pathological analysis) are still possible. In an effort to tackle his last obstacle we require the final diagnosis to be shared by two independent, blinded, experienced movement disorders specialist neurologists.

We included SPECT scans in the study to enable us to make a direct comparison between SPECT and TCD as to their diagnostic accuracy. Although the use of SPECT scans in the diagnostic work-up of parkinsonian patients is still debated, it is widely used [8,19,46]. We feel that this will add to the clinical relevancy of our study results. Additionally, contributions of tests for smell, depression, cognition, in the diagnostic process can be assessed also.

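### The rule for non-identical final diagnoses discards patients whom both specialists call non-PD, and the target of 250 makes no allowance for inconclusive reference diagnoses

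*Protocol article*

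**What the plan says.** Section E of the protocol article has each patient re-examined after two years by two movement disorder specialists. They work separately, blinded to the test results and to the treating neurologist's records: "they will be asked to reach a clinical diagnosis, independently from each other, according to generally accepted clinical criteria". The rule for disagreement is "If these two diagnoses are not identical, the final diagnosis of this patient will be coded as inconclusive". No later step resolves such a case.

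The abstract describes the reference standard as a "consensus clinical diagnosis reached by two independent, blinded, movement disorder specialist neurologists after 2 years follow-up". The Discussion puts it as "we require the final diagnosis to be shared by two independent, blinded, experienced movement disorders specialist neurologists", and concedes that "there will always remain a small proportion of patients that is not definitely diagnosable after two years".

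Under Data analysis the main hypothesis is that "TCD is as sensitive as SPECT to differentiate PD from other parkinsonian disorders". Accuracy is planned for PD against atypical syndromes (APS), essential tremor, vascular parkinsonism (VP), drug-induced parkinsonism (DIP), and all other types together. The sample size starts from 190 and is inflated twice, for a 15% share of insufficient bone windows and for a 90% share with final PD, to reach 250.

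**The concern.** The rule demands more agreement than the main analysis uses. PD against all other types needs only a PD or non-PD label. A patient called VP by one specialist and DIP by the other has an agreed non-PD status, yet on the wording of section E becomes inconclusive and has no cell in the table. The same holds for a patient called MSA by one and PSP by the other, although Data analysis pools these as APS and no planned contrast separates them.

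The loss falls on the smallest group, the one that supplies specificity and much of the information in the predictive values. In addition, if patients still disputed at two years are left out, and the tests perform less well in them, the reported accuracy will be somewhat too favourable. Finally, a source of loss that the Discussion itself foresees is not carried into the sample size.

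**Working it through.** **Does any planned contrast accommodate an inconclusive patient?** The five contrasts each set PD against a named non-PD class or against all other types. None has an inconclusive category. The article does not say in words that such patients are excluded; that follows from the contrasts as listed.

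**How specialist pairs fare under the rule as worded:**

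| Pair | Identical? | Agreed for PD v. all others? | Agreed for PD v. APS? |
|---|---|---|---|
| VP / DIP | no | yes, both non-PD | not applicable |
| MSA / PSP | no | yes, both non-PD | yes, both APS |
| PD / MSA | no | no | no |

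Only the last row is a disagreement that matters to the main contrast.

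**Reproducing the size chain (inputs from Data analysis: 190, 15%, 90%).**
- 190 / 0.85 = 223.5, rounded up to 224, as stated.
- 224 / 0.90 = 248.9, rounded up to 249, against the stated 250. This reproduces.
- Expected evaluable PD patients: 250 × 0.85 × 0.90 = 191.25, about one more than the 190 needed. Nothing is left for inconclusive reference diagnoses, deaths or losses over two years.

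**Size of the non-PD group.** 250 × 0.10 = 25 patients, of whom 25 × 0.85 = 21.25 have a usable bone window. Each patient discarded is 1 / 21.25 = 4.7% of that group.

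**Effect on precision.** The documents give no rate of non-identical diagnoses or loss, so q is an assumption, applied equally to both groups. The Wald lower limit is 0.90 − 1.96 × √(0.09 / n), with n = 191.25 × (1 − q).

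| q | Evaluable PD | Lower limit | Evaluable non-PD |
|---|---|---|---|
| 0% | 191 | 85.7% | 21.3 |
| 10% | 172 | 85.5% | 19.1 |
| 20% | 153 | 85.2% | 17.0 |

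The rule and other losses together cost about 0.2 to 0.5 percentage points of the lower limit. The limit is already below 86% with no loss, because 190 does not follow from the stated standard error: 0.09 / 0.02² = 225. That is a separate matter.

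**Direction of selection.** If sensitivity is s₁ in agreed PD cases and s₂ in PD cases coded inconclusive, the analysed set shows s₁, while all PD cases together would show s₁(1 − q) + s₂q. The overstatement is q(s₁ − s₂). Neither q nor s₂ can be taken from the documents, so no figure is put on it.

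**The case against.** - **The strict rule is deliberate and disclosed.** The Discussion requires a shared diagnosis in order to limit misdiagnosis and accepts that some patients will stay undiagnosed. This stands as a reason not to replace independent agreement with a discussion. It does not justify losing patients whose non-PD status is agreed.
- **Exclusion is nowhere stated, and an analysis plan may deal with these patients.** This is fair, and is why the point rests on how section E fixes the coding, set against the contrasts listed. Section E also does not define the level at which diagnoses must be identical. Since MSA and PSP are pooled as APS, that example could be read either way; VP and DIP are the clearer case.
- **TCD and SPECT are done in the same patients.** A missing reference diagnosis removes the patient from both, so the comparison between tests need not be biased. That is correct, but each test's own sensitivity and specificity are also reported, and specificity still loses patients.
- **Some losses are already covered.** Excluding patients with a life expectancy under two years is a partial safeguard against deaths. The 90% might mean confirmed PD, with inconclusive cases inside the other 10%. The text does not say so, and that reading would leave fewer than 25 non-PD patients.

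Two stronger readings are tempting but not supported. A reader might infer that the consensus in the abstract contradicts section E. Consensus reached by independent specialists can simply mean concordance, and the Discussion's wording fits that; it is loose phrasing. A reader might also infer that the rule brings back the bias of earlier studies in well-defined, later-stage patients. It does not: entry bars "Patients presenting with a clear unequivocal diagnosis of their parkinsonism", the tests are done within six weeks, and patients unclear at entry but agreed at two years stay in.

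**Conclusion.** The point holds in a limited form. On its wording, the identity rule discards patients on whom the main contrast is settled, from a group of only about 21 evaluable non-PD patients. This rests on the protocol's own 90% and 15%, and on reading identical at the level of the named disease.

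The sample size has no allowance for inconclusive reference diagnoses or two-year losses, but the effect on precision is modest: from 85.7% to 85.5%–85.2% at an assumed 10–20% loss. If disagreement is mostly among non-PD subtypes, the PD loss is smaller than that and the non-PD loss larger.

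Some upward selection of accuracy is possible. A reader might be drawn to a figure of several points by assuming a much lower sensitivity in disputed cases, but the documents supply neither that sensitivity nor the share disputed. Nor is the gap between 90% and 86% a tolerance for bias: 86% is a target for a confidence limit.

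**What to change.** 1. In section E, define concordance at the level of each contrast: both PD or both non-PD for PD against all other types; both PD or both APS for PD against APS; the same specific diagnosis only where a contrast needs it. Keep the two independent diagnoses on file for agreement statistics.
2. For patients on whom the specialists differ on PD versus non-PD, add a sensitivity analysis that counts them once as PD and once as non-PD.
3. Under Data analysis, state an assumed share lost to inconclusive diagnoses and follow-up, and restate the expected number of evaluable PD patients and the lower limit under it, as in the table above. The small loss of precision does not by itself call for more enrolment.
4. In the abstract, where the text reads "As a surrogate gold standard we will use the consensus clinical diagnosis reached by two independent, blinded, movement disorder specialist neurologists", use wording that matches the concordance rule.

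A blinded discussion of discordant cases is optional. It would recover some patients at the price of a less certain diagnosis; if it is used, report results with and without it.

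The cost of items 1 to 4 is wording and one extra analysis, with no new visits, staff or data. Item 1 should be settled before the final diagnoses are compared with the test results.
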